#### Direct and indirect costs

*Can participation in the PNP program reduce direct costs for out- and inpatient treatment and costs of medication due to the focus diagnoses?*

ii.a.) We expect costs for out- and inpatient treatment and costs of medication due to the focus diagnoses to be lower among patients in IG-PNP compared to costs for out- and inpatient treatment and costs of medication due to the focus diagnoses among patients in CG-GP as well as CG-UC.

*Can participation in the PNP program reduce indirect costs,* i.e.*, the number of days of incapacity to work due to the focus diagnoses?*

ii.b.) We expect the number of days of incapacity to work and amount of sick pay due to the focus diagnoses to be lower among patients in IG-PNP compared the number of days of incapacity to work and amount of sick pay due to the focus diagnoses among patients in CG-GP as well as CG-UC.

In order to evaluate the direct and indirect costs, we will analyze retrospective secondary data from 2014, 2015, and 2016. Therefore, we will conduct a quasi-experimental study to compare costs caused by service utilization and by sick pay over a period of 12 months between IG-PNP and CG-GP, CG-UC.

#### Level of detail of diagnoses

Is the *amount of specifc diagnoses higher during the treatment process in the PNP program compared to the control group CG-GP and to the control group CG-UC?*

iii.a.) We expect health care providers to submit a higher percentage of specific depression diagnoses (with determination of the degree of severity) in proportion to unspecific depression diagnoses for patients in IG-PNP to the statutory health insurance compared to CG-GP as well as CG-UC.

In order to determine the amount of specific diagnoses, we will also use retrospective secondary data from 2014, 2015 and 2016. Therefore, we will use a trend analysis of diagnoses, stratified according to the intervention and control groups.

#### Structural and process quality

*How do health care providers within the PNP program evaluate the PNP program?*

This is an exploratory evaluation without specific hypotheses.

We will conduct a mixed-methods study with an exploratory sequential design [29] to evaluate the structure and process quality of the PNP program. Therefore, we will include GPs, medical specialists, and psychotherapists working in the PNP program. First, we will conduct semi-structured qualitative interviews with purposefully sampled [30] health care providers working in the PNP program. Second, we will develop an evaluation instrument specific for the PNP program based on the analyzed interviews. Third, all health care providers working in the PNP program will receive this paper-pencil instrument. The present study protocol was prepared in accordance with SPIRIT guidelines [31]. The SPIRIT checklist can be found in Additional file 1.

### Inclusion and exclusion criteria

#### Patients

We will include patients in the study who will be on sick leave due to one of the following eight mental or neurological disorders at the first time during the previous 12 months: bipolar disorders (F31.x), depressive disorders (F32.x, F33.x, F34.1), anxiety disorders (F40.x, F41.x), adjustment disorder (F43.2), somatoform disorders (F45.x), alcohol abuse disorders (F10.x), schizophrenia (F20.x) or multiple sclerosis (G35.x). In addition, patients will be eligible, if they are insured by the AOK BW, are at least 18 years old, and are treated by a health care provider licensed in Baden-Wuerttemberg, Germany. We will exclude patients if they have a legal guardian. Additionally, patients will be excluded if they were on sick leave due to a similar diagnosis to their inclusion diagnosis within the 12 months before the index episode of sick leave. Consequently, mentally ill patients will be excluded if they were on sick leave due to a mental or behavioral disorder (Fxx.x) and patients with multiple sclerosis will be excluded if they were on sick leave due to a G35.x-diagnosis within the last 12 months. Patients choose their contract status (PNP program, “general practitioners program”, usual care) based on their preference.

#### Health care providers

##### Qualitative survey

We will conduct purposeful sampling [30] to cover different perspectives on the PNP program. Therefore, we will include nine interview partners from the three involved health care provider groups (GPs, specialists, psychotherapists). Within the groups of GPs and psychotherapists, we will include interview partners qualified in providing psychodynamic, psychoanalytic, or cognitive behavioral psychotherapy. Within the group of specialists, we will include interview partners enrolled in each of the three modules of the PNP program, namely neurology, psychiatry, and psychotherapy. To focus on potential chances and challenges of combined modules, we will include at least one specialist enrolled in all three modules. Furthermore, we will focus on heterogeneity regarding region, duration of PNP-participation, and gender.

##### Quantitative survey

We will include all health care providers working with adult patients within the PNP program. In February 2018, *N* = 698 health care providers were enrolled in the program.

### Outcome measures

Outcome measures are shown in Table 2.

**Table 2 Tab2:** Lists of outcome measures

Outcomes	Instruments
*Patient-related primary data*	
*Primary outcomes*	
Health-related quality of life	Short-form health survey (SF-36), mental component summary score [39]
*Secondary outcomes*	
Health-related quality of life	Short-form health survey (SF-36), physical component summary score [39], EuroQol-5D (EQ-5D) [40]
Depressive symptoms	Patient Health Questionnaire – Depression Module (PHQ-9) [41]
Anxiety symptoms	Patient Health Questionnaire – Generalized Anxiety Disorder Module (GAD-7) [42]
Somatoform symptoms	Somatic Symptom Scale – 8 (SSS-8) [43]
Alcohol consumption	Alcohol Use Disorders Identification Test (AUDIT) [44]
Schizophrenic symptoms	Eppendorfer Schizophrenia Inventory – Short Version (ESI-K) [45]
Adjustment disorder-symptoms	Adjustment Disorder-New Module 20 (ADNM-20) [46, 47]
Physical and psychological impact of multiple sclerosis	Multiple Sclerosis Impact Scale (MSIS-29) [48, 49]
Patient satisfaction with outpatient care	Satisfaction with ambulatory care (ZAPA) [50]
*Patient-related secondary data*	
*Primary outcomes*	
Direct costs caused by outpatient and inpatient service utilization and medication within one year following diagnosis	Claims data about outpatient and inpatient service utilization and medication
*Secondary outcomes*	
Indirect costs caused by productivity losses	Days of incapacity to work and sick pay
Level of detail of depression diagnoses	Claims data about diagnoses (specific: F32.0-F32.3, F33.0-F33.4; unspecific: F32.8, F32.9, F33.8, F33.9)
*Health care provider-related primary data*	
Aspects of the PNP program - access - reasons for participation - barriers to participation - advantages and disadvantages of participation - differences in health care - appropriateness of compensation - organizational aspects - interprofessional cooperation - evaluation and use of contract components	Questionnaire on structure and process quality of the PNP program, in-house development based on - qualitative interviews with selected health care providers - a questionnaire from another project (see [51])

### Data collection process

#### Patient-related primary data

The statutory health insurance company (AOK BW) will organize the recruitment in the area of Baden-Wuerttemberg, Germany. First, the statutory health insurance will identify all patients, who meet the inclusion criteria. The statutory health insurance will send information letters, informed consent sheets, and the baseline questionnaires to these patients. Only participants who give their informed consent will be included in the study. Patients, not sending back questionnaires and informed consent sheets, will receive one reminder. The statutory health insurance will transfer group membership and routine diagnoses to the research institution. Twelve month after baseline, participants will receive the follow-up questionnaire. Participants will receive 15 Euro for sending both questionnaires to the UKE.

#### Patient-related secondary data

The statutory health insurance will deliver routinely collected administrative health data retrospectively for 2014, 2015, and 2016 to the research institution.

#### Health care providers-related primary data

To develop a questionnaire for all health care providers within the PNP program, we will interview selected health care providers within the PNP program. Given willingness to participate and obtained informed consent, we will conduct face-to-face-interviews at health care providers’ offices. We will record, transcribe, and anonymize the interviews. We will qualitatively analyze anonymized transcripts in order to prepare a quantitative questionnaire for all health-care providers enrolled in the PNP program. Finally, we will send a study information, informed consent sheets, and this questionnaire to all health care providers within the PNP program. Health care providers will receive financial compensation for participation.

### Sample size calculation

The sample size was calculated for being able to detect a clinically relevant effect regarding the primary outcome health-related quality of life (SF-36) between IG-PNP and control groups CG-GP and CG-UC. Meta-analyses [19, 21, 32] calculated small to moderate effect sizes for collaborative care models. According to Cohen, a small to moderate effect size is defined as d = 0.30 [33]. Given an expected correlation of *r* = 0.4 between outcome at baseline and at follow-up, we will need *n* = 441 patients (*n* = 147 per group) to detect this effect with α = 0.05, power of 0.80 and without the random effect of health care providers offices [34]. Given an expected intraclass correlation of *p* = 0.10 and 100 health care providers in each group, we multiplied the necessary sample size with the design effect of DEF = 1.047 (1 + (147/100–1)*0.10) in consideration of random effects. Consequently, we need to include *n* = 153 patients per group (460 patients in total) in the analyses. We plan to overrecruit by 16.5% to compensate losses of statistical power through possibly different group sizes (IG- PNP ≈ 27%, CG-GP ≈ 22%, CG-UC ≈ 51%) with an allocation ratio of 2.33. Accordingly, we aim to include 536 patients in the analyses. Based on experiences, we expect a response rate of 7% for baseline. We expect dropout rates 40% for follow-up assessments. Consequently, we plan to contact *n* = 12,800 patients to receive data from *n* = 538 patients. We will perform dropout analyses for both study dropout and intervention dropout.

For analyzing direct and indirect costs (ii) and level of detail of diagnoses (iii), we will use complete secondary data from all patients meeting the inclusion criteria in 2015. Because of the exploratory approach, we did not conduct a formal sample size calculation for the evaluation of structure and process quality (iv).

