### Research questions, hypotheses and study design

#### Effectiveness

*Is treatment within the PNP program more effective compared to the treatment in the control groups (CG-GP, CG-UC) with regard to health related quality of life among patients with mental or neurological disorders (main research question)?*

i.1.) We expect higher scores of health-related quality of life for the IG-PNP compared to the control group CG-GP and to the control group CG-UC.

i.2.) We expect higher scores of functional health, lower illness-specific symptom burden as well as higher patient satisfaction for the IG-PNP compared to CG-GP as well as CG-UC.

*Which groups of patients benefit most from the PNP program?*

i.3.) We expect patients with chronic and severe focus diagnoses to benefit most from the PNP program. Accordingly, we expect chronicity (illness duration) and degree of severity to be significant moderators of the interaction effect. We will investigate additional moderators like gender, age, educational status, diagnoses and comorbidity.

We will conduct a prospective non-randomized controlled trial among patients to answer research questions related to effectiveness. We will include consecutively recruited patients belonging to the three groups (IG-PNP, CG-GP, CG-UC). We will measure health-related quality of life, patient-relevant symptom severity and satisfaction with care at baseline (t_0_, date of sick leave) and at 12-month follow-up (t_1_). Although randomized controlled trials could provide the best evidence in evaluation studies [28], we cannot randomize participants to the three groups for ethical and contractual reasons. In order to prevent the selection bias, we will recruit participants for all three groups in the same area in Germany (Baden Wuerttemberg). We will use entropy balancing to control for potential differences between intervention and control groups. No independent data monitoring committee to determine if the study should be modified or discontinued is necessary, because patients receive interventions irrespective of study continuation or participation. We will monitor and document study responses and discuss possible adaptions if necessary.

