### Statistical analysis

We will use entropy balancing [35, 36] to control for differences between IG-PNP, CG-GP, and CG-UC in primary and secondary data. This method constructs balancing weights for each control observation such that the reweighted control groups match the covariate moments in the intervention group. The weights are based on patient characteristics (e.g. age, gender, region, type of insurance (compulsorily or voluntarily), costs of service utilization, mental comorbidity, and the Combined Comorbidity Index (CCI) [37] from ICD-10 for inpatient stays). The CCI is based on the ICD-10 codes belonging to the hospital stays, in order to take the severity of somatic comorbidities into account.

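### The stated 80% power is for an unweighted analysis; no term covers the entropy-balancing weights, so 80% is not secured for both contrasts in the main hypothesis

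*Protocol article*

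**What the plan says.** In the protocol article, the section Sample size calculation starts from "a small to moderate effect size is defined as d = 0.30". The baseline adjustment rests on this input: "Given an expected correlation of *r* = 0.4 between outcome at baseline and at follow-up". The resulting number is printed as "we will need *n* = 441 patients (*n* = 147 per group", and the target it serves is "to detect this effect with α = 0.05, power of 0.80 and without the random effect of health care providers offices". The clustering step has its own assumptions: "Given an expected intraclass correlation of *p* = 0.10 and 100 health care providers in each group". On that basis the authors write "we multiplied the necessary sample size with the design effect of DEF = 1.047". That gives 153 per group and 460 in total. A further 16.5% is added for group shares of about 27% (IG-PNP), 22% (CG-GP) and 51% (CG-UC), giving 536 analysed. The number to contact then follows from a 7% response and 40% dropout.

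On the analysis, the opening of Statistical analysis applies entropy balancing to the survey data and the claims data alike, and describes it so: "This method constructs balancing weights for each control observation such that the reweighted control groups match the covariate moments in the intervention group". Confirmation for the survey study stands in the Effectiveness part of the research questions: "We will use entropy balancing to control for potential differences between intervention and control groups". The examples of balancing characteristics include age, gender, region, type of insurance, service costs, mental comorbidity and a comorbidity index. The Effectiveness paragraph under Statistical analysis adds further covariates to the mixed model only where needed, for instance under substantial imbalance. The main hypothesis names two contrasts: IG-PNP against CG-GP and IG-PNP against CG-UC.

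**The concern.** Weighted control means are less precise than unweighted ones unless all weights are equal. To a first approximation, the variance of a control mean is multiplied by the Kish factor K = n·Σw²/(Σw)², which is 1 for equal weights and above 1 otherwise. The plan has reason to expect unequal weights: patients choose their contract status, and the Discussion concedes possible selection bias.

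The sample size section lists every allowance it makes, and weighting is not among them. The 16.5% is explicitly assigned to group sizes, so on the plan's own account nothing is held in reserve. A non-significant weighted result could then be read as coming from a study with 80% power for d = 0.30 when the power of that comparison was lower. The more the groups differ, the more the weighting is needed and the larger the loss.

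**Working it through.** **Inputs from the sample size section:** d = 0.30; r = 0.4; α = 0.05 (two-sided reproduces the plan's figure); power 0.80; clustering factor 1.047; 536 analysed; shares 27/22/51%. **Assumed:** K, because the documents give no weight variance.

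**1. Reproducing the plan.**
- 2 × (1.960 + 0.842)² / 0.30² = 174.4 per group without baseline adjustment.
- 174.4 × (1 − 0.4²) = 146.5, so 147 per group.
- 147 × 1.047 = 153.9 (stated 153). 146.5 × 1.047 × 3 = 460.2 (stated 460).
- 460 × 1.165 = 535.9 (stated 536).

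Other formulas do not give 147: a change score gives 210, no baseline adjustment 175, a one-sided test 116. The calculation is an unweighted two-group ANCOVA with two inflations, and its arithmetic stands.

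**2. Power with weighted controls.** With K on the control group only:

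Power = Φ(0.30 / √[0.84 × 1.047 × (1/n₁ + K/n₂)] − 1.96)

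Projected sizes: 0.27 × 536 = 144.7 (IG-PNP), 0.22 × 536 = 117.9 (CG-GP), 0.51 × 536 = 273.4 (CG-UC).

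Example, CG-GP at K = 1.3: 0.84 × 1.047 × (1/144.7 + 1.3/117.9) = 0.0158; square root 0.1256; 0.30/0.1256 = 2.389; Φ(2.389 − 1.96) = 66.6%.

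| Comparison | K = 1.0 | K = 1.3 | K = 1.5 | K = 2.0 |
|---|---|---|---|---|
| IG-PNP vs CG-GP (145 vs 118) | 73.2% | 66.6% | 62.7% | 54.4% |
| IG-PNP vs CG-UC (145 vs 273) | 87.5% | 84.2% | 81.9% | 76.5% |
| Equal groups, 153 each | 79.9% | 74.2% | 70.6% | 62.7% |

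Against CG-UC, power reaches 80% at K of about 1.68. Against CG-GP it is below 80% at every K of 1 or more.

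**3. Is K of 1.3 to 1.5 plausible?** Entropy balancing was simulated on the means of seven independent normal covariates, 154 against 154, each shifted by the same standardised difference. The mean K was 1.10 with no true difference, 1.19 at 0.10 SD, 1.30 at 0.15 SD, 1.49 at 0.20 SD and 2.1 at 0.30 SD. These scenarios are illustrations. If only three of the seven covariates differ by 0.15 SD, K is about 1.18.

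**4. Possible offset.** If the balancing variables explain a further 10% of residual variance (an assumption), the variance is multiplied by 0.9:

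| Comparison | K = 1.0 | K = 1.3 | K = 1.5 |
|---|---|---|---|
| vs CG-GP | 77.6% | 71.2% | 67.2% |
| vs CG-UC | 90.7% | 87.7% | 85.7% |
| 153 each | 83.9% | 78.5% | 75.1% |

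The gain is about 3 to 5 points in each cell. The CG-UC threshold moves from about 1.7 to about 2.1.

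**The case against.** The strongest case against the point has four parts.

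- **Nothing is miscalculated.** The plan's figures reproduce within rounding. This stands: the fault is an omitted term.
- **The size of the loss is unknown.** The documents give neither weight variance nor group imbalance, and the simulated scenarios are constructed. This stands, and is why only a range is given.
- **Weights alone do not break 80% at modest imbalance.** A reader might infer that weighting takes power below 80% throughout. The documents do not support that. At the projected sizes, CG-UC starts at about 88% and stays above 80% until K is about 1.7. CG-GP is already at 73% through the group split, and weighting only deepens that shortfall. The fall from 80% to 71% at 153 per group describes a layout the plan does not expect.
- **Precision may be recovered.** The Kish factor ignores what is gained by balancing prognostic variables. With a further 10% of variance explained, 153 per group at K = 1.3 comes back to about 79%, and a stronger gain could cancel the loss there. It does not bring CG-GP to 80% at the projected sizes.

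One might also say that a condensed article leaves weighting details to an analysis plan. That holds for the weighted-model specification. It does not hold for the power figure, because the article prints the whole calculation with each allowance named, and states a power that the planned analysis is not shown to have.

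**Conclusion.** The point holds in a limited form. The 80% power for d = 0.30 was derived for an unweighted analysis and adjusted only for clustering and group sizes, while the planned comparison weights every control patient. The plan therefore does not secure 80% for both contrasts of its main hypothesis.

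For K between 1.3 and 1.5, weighting costs about 7 to 11 points against CG-GP (from 73% to 67–63%) and about 3 to 6 points against CG-UC (from 88% to 84–82%). These figures rest on an assumed K, a common clustering factor of 1.047, the projected shares of 536 and the Kish approximation. Prognostic balancing variables could return several points. The part of the CG-GP shortfall that precedes weighting is due to the group split and should not be attributed to the weights.

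**What to change.** No change to enrolment is needed.

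1. In Sample size calculation, state an assumed weighting design effect, as a range, for each control group. Restate power separately for the two contrasts at the expected shares. For example: with an assumed design effect of 1.3 to 1.5 from the weights, 536 analysed patients give about 63–67% power for d = 0.30 against CG-GP and about 82–84% against CG-UC, before any gain from prognostic covariates.
2. In the Effectiveness paragraph of Statistical analysis, keep the balancing covariates as fixed effects in the weighted mixed model in all cases, not only under imbalance. This recovers part of the lost precision.
3. Report each control group's effective sample size with the primary result.

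The 2015 claims cohort can give a first value of K, but only as a rough guide: the survey sample is a 7% response with 40% dropout and may be balanced differently.

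The cost is protocol or SAP wording and a short calculation on data the study will already receive. The downside is that the stated power becomes less favourable.

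### The 16.5% over-recruitment leaves power for IG-PNP versus CG-GP at about 73%, not 80%, at the plan's own group split

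*Protocol article*

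**What the plan says.** The Sample size calculation section sizes the trial on the SF-36 difference between IG-PNP and the control groups CG-GP and CG-UC. Its inputs are an effect for which "a small to moderate effect size is defined as d = 0.30", a baseline adjustment ("Given an expected correlation of *r* = 0.4 between outcome at baseline and at follow-up"), and a sample large enough "to detect this effect with α = 0.05, power of 0.80". From these it states "we will need *n* = 441 patients (*n* = 147 per group"). A design effect of 1.047 raises this to 153 per group, 460 in total.

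The section then turns to unequal groups: "We plan to overrecruit by 16.5% to compensate losses of statistical power through possibly different group sizes". It gives expected shares of about 27% IG-PNP, 22% CG-GP and 51% CG-UC, "with an allocation ratio of 2.33", and concludes: "Accordingly, we aim to include 536 patients in the analyses". The 536 is net of non-response and dropout.

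Hypothesis i.1, in the Effectiveness part of the research questions, expects a better outcome in IG-PNP than in each control group, named separately. For the analysis, the Statistical analysis section says of entropy balancing: "This method constructs balancing weights for each control observation such that the reweighted control groups match the covariate moments in the intervention group".

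**The concern.** The calculation is for one pairwise comparison with equal groups. When the three groups differ in size, the effect on power depends on which pair is compared. Just over half of the analysed patients are expected in CG-UC, and they add nothing to IG-PNP versus CG-GP. At 536, both groups in that comparison are below the 153 that the plan itself requires, so power must be below the stated level.

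The comparison matters. In Table 1, CG-GP patients have the general practitioners program without the PNP program, so this contrast shows what PNP adds to it. If readers take the design to have 80% power there, they will give a null result more weight than it deserves.

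**Working it through.** **Inputs, all from the Sample size calculation section.** d = 0.30; r = 0.4; α = 0.05; power 0.80; design effect 1.047; shares 0.27 / 0.22 / 0.51; 536 analysed. Sidedness is not stated. Two-sided is used because it reproduces the plan's figure.

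**1. Reproduce the base.** n per group = 2 × (1.96 + 0.8416)² × (1 − 0.4²) / 0.30² = 146.5, rounded up to 147. This matches. Variants that do not match: one-sided 116, no baseline adjustment 175, change score 210, two-sided α of 0.025 178.

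**2. Reproduce the clustering step.** 1 + (147/100 − 1) × 0.10 = 1.047. 146.5 × 1.047 = 153.4 per group, and 3 × 153.4 = 460. Power with 153 per group and this design effect is 79.9%. The chain is sound up to here.

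**3. Reproduce the final target.** 460 × 1.165 = 535.9, i.e. 536. The mailing agrees: 12,800 × 0.07 × 0.60 = 537.6, i.e. 538.

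**4. Group sizes at 536.** 536 × 0.27 = 144.7; 536 × 0.22 = 117.9; 536 × 0.51 = 273.4.

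**5. Power per comparison.** SE = √[0.84 × 1.047 × (1/n₁ + 1/n₂)] and power = Φ(0.30/SE − 1.96).

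| Comparison | n₁ / n₂ | SE | Power | Detectable d at 80% |
|---|---|---|---|---|
| IG-PNP vs CG-GP | 144.7 / 117.9 | 0.1163 | 73.2% | 0.326 |
| IG-PNP vs CG-UC | 144.7 / 273.4 | 0.0964 | 87.5% | 0.270 |

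The detectable effect is 2.8016 × SE. With a design effect computed from each group's own size, the powers are 73.9% and 86.2%. With no design effect at all, power against CG-GP is still only 75.1%.

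**6. Inflation that would be needed.** With equal thirds, 1/n₁ + 1/n₂ = 6/N, so the factor on 460 is (1/share₁ + 1/share₂)/6.

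- Against CG-GP: (1/0.27 + 1/0.22)/6 = 1.375. The required total is (1/0.27 + 1/0.22) × 0.84 × 1.047 × 2.8016² / 0.09 = 632.7, i.e. about 633 analysed (171 / 139 / 323). At the plan's response and dropout rates that is 633 / (0.07 × 0.60), about 15,100 letters instead of 12,800.
- Against CG-UC: (1/0.27 + 1/0.51)/6 = 0.944, so no inflation is needed.

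**7. The 16.5% and the 2.33.** The usual two-group inflation at allocation ratio k is (1 + k)²/(4k). At k = 2.33 it is 3.33² / 9.32 = 1.190, i.e. 19.0%. The section does not say which groups the ratio relates.

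**The case against.** **The 0.80 belongs only to the equal-group step.** The section never states outright that each comparison keeps 80% at unequal sizes. The mean of the two required factors is (1.375 + 0.944)/2 = 1.159, or about 533 patients, close to 536, and mean power across the two comparisons is about 80.4%. The 16.5% may therefore be an average rather than a slip. The text does not say so, however, and i.1 names the control groups separately. An average does not deliver the intended power where it is lower.

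**Other readings reach 80% at 536.** Pooling the controls gives about 91%, a three-group omnibus test about 84% if both controls have the same mean, and a one-sided test 82.5%. Pooling and the omnibus test do not answer i.1. A one-sided test would have produced 116 per group, not 147.

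**The gap is modest and the shares approximate.** This stands. The shortfall is about 7 points on one of two comparisons, and rounding in the shares moves it only between about 72% and 74%. The pooled effects of 0.34 and 0.35 cited in the Background would give about 83% to 85% against CG-GP. But those are for symptoms, not the SF-36, and the plan chose 0.30.

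**Readings that go further than the documents.** A reader might infer that 2.33 is CG-UC to CG-GP, since 51/22 = 2.32, and so describes a pair with no hypothesis. It also equals 70/30, and the derivation is not given. A reader might also put a figure on the further loss from weighting. The documents give no weight distribution, and balancing covariates that predict the outcome can recover some precision, so no figure is supported.

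**Conclusion.** The power stated for IG-PNP versus CG-GP is wrong as written. At 536 analysed patients and the plan's own split it is about 73%, against about 88% for CG-UC. The chance of missing a true d = 0.30 against CG-GP is thus about 27% rather than 20%, and the effect detectable with 80% power is about 0.33. The added 16.5% does not make up the loss, which would need about 37.5%, and it does not follow from the printed ratio.

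This rests on the stated shares being realised, on r = 0.4 and the design effect of 1.047, and on a two-sided test. All figures are before weighting.

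A reader might infer that the primary analysis is unsound or that a null result is bound to be misread. Neither follows: no estimate or test becomes invalid, and nothing in the protocol says that a null result will be taken as equivalence. The point should be corrected, but it does not undermine the design.

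**What to change.** In the Sample size calculation section:

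1. State power or detectable effect for each comparison at the expected split: about 73% (d ≈ 0.33 at 80% power) against CG-GP and about 88% (d ≈ 0.27) against CG-UC.
2. Correct or explain the 16.5%, and say which groups the 2.33 relates.
3. Note that these figures are before entropy-balancing weights.
4. Say that a null result against CG-GP will be reported with its confidence interval and read in the light of the lower power.

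This costs one paragraph and no patients. Keeping 80% against CG-GP at the same split would cost about 97 more analysed patients (633 − 536), or roughly 2,300 more letters (15,100 − 12,800).

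Sending a larger part of the same 12,800 letters to IG-PNP and CG-GP is at most an option to consider. It requires enough eligible CG-GP patients. It must also be reconciled with the consecutive recruitment in the Effectiveness part and with the Data collection process section, under which all patients who meet the criteria are identified and mailed. Any gain assumes that the overall 7% response and 40% dropout hold in each group, and it too would be before weighting.
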